### Blinding

This study will implement a double-blind design in which participants and investigators will be blinded to treatment allocation. The statistician will not be involved in randomization and will analyze data without having access to information about allocation. Treatment allocation will be disclosed after the conclusion of the trial except in cases of emergency, such as severe AEs. Both TSF and placebo are manufactured as fine brown granules and packaged in packets identical in appearance. When dissolved in warm water, the taste, smell, and appearance of the TSF and placebo are identical. Investigators and participants will be unaware of the drug allocation.

### Statistical analysis

This trial will use three analysis sets: the intention-to-treat set, which will regard all participants as randomized regardless of whether or not they received the randomized treatment; the per protocol analysis set, which will be restricted to participants who complete the 24-week treatment and/or have the primary endpoint measurement records of at least three time points during the study; and the safety analysis set, which will include randomized participants who have made at least one visit. Multiple imputation analysis will be performed to account for the effect of missing data. Partially missing data will be carried forward with the principle of the last observation carried forward (LOCF). A *P* value less than 0.05 will be considered significant. SAS 9.2 software (SAS Institute, Cary, NC, USA) will be used for analysis.

Continuous variables will be expressed as the mean (SD), and categorical variables, as numbers and percentages. To compare baseline data between the two groups, independent *t* tests (or the Mann–Whitney U test) will be used to analyze continuous data, and chi-square or Fisher exact test will be used for categorical data. Outcome analysis will be performed using *t* test for normally distributed data and rank sum test for non-normal distribution data. Considering that the baseline 24 h UP and/or A1C are essential for the progression of urinary protein, analysis of covariance (ANCOVA) using 24 h UP and/or A1C as covariates will be performed to analyze the 24 h UP reduction at 24 weeks. To investigate the effects of treatment and time course, repeated measures analysis of variance (ANOVA) will be applied to determine changes in the 24 h UP and eGFR at each visit. For safety endpoints, incidences of DILI and BMS will be analyzed by Kruskal-Wallis test, and the incidence of QTc will be evaluated by a chi-square test. For AE evaluation, all AEs will be reported including its grade, time of occurrence, duration, treatment, prognosis, and correlation with the intervention drugs. The chi-square test or Fisher exact test will be used to compare the incidence of AEs between the two groups.

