### Study visits and assessment

Study duration will be 50 weeks, comprised of a 2-week run-in period, 24 weeks of intervention, and 24 weeks of follow-up. After treatment commences, visits will occur every 4 weeks during the intervention period. During the follow-up period, participants will be asked to visit at 28, 36, and 48 weeks. An overview of specific measurements and time points of data collection can be found in Table 3.

**Table 3 Tab3:** Schedule of enrollment, allocation, visits, and assessments

	Study Period										
	Enrollment	Allocation	Intervention						Follow-up		
Time point (weeks)	−2	0	4	8	12	16	20	24	28	36	48
Eligibility screen	√										
Written informed consent	√										
Medical history	√										
Physical examination		√	√	√	√	√	√	√			
Routine blood and urine		√		√		√		√			
Electrocardiogram		√		√		√		√			
ALT, AST, ALP, GGT, TBIL		√		√		√		√			
24 h urinary protein		√	√	√		√		√	√	√	√
Serum Cr, eGFR		√	√	√		√		√	√	√	√
TC, TG, LDL-C, HDL-C		√	√	√		√		√			
A1C, CRP		√		√		√		√			
Evaluation of TCM syndrome		√	√	√	√	√	√	√	√	√	√
Drug distribution		√	√	√	√	√	√				
Retrieval of unused drugs			√	√	√	√	√	√			
Adverse events			√	√	√	√	√	√	√	√	√

*Abbreviations*: *A1C* hemoglobin A1C, *ALP* alkaline phosphatase, *ALT* alanine transaminase, *AST* aspartate aminotransferase, *eGFR* estimated glomerular filtration rate, *GGT* gamma-glutamyl transpeptidase, *LDL-C* low-density lipoprotein cholesterol, *serum Cr* serum creatinine, *TBIL* total bilirubin, *TC* total cholesterol, *TCM* traditional Chinese medicine, *TG* triglycerides, *HDL-C* high-density lipoprotein cholesterol

√ = Action items

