### Outcome measurements

#### Primary endpoint

The primary endpoint is 24 h UP. The change in 24 h UP from baseline to 24 weeks will be the analysis metric for the difference between the two groups. At baseline and treatment endpoint (24 weeks), the average values of two different samples collected within 1 week will be used to minimize variation between the different urine samples.

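### Multiple imputation and LOCF are both prescribed without saying which one produces the week-24 primary result, and LOCF on its plain reading can bias it

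*Protocol article*

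**What the plan says.** The protocol article defines the primary comparison under Primary endpoint: "The change in 24 h UP from baseline to 24 weeks will be the analysis metric for the difference between the two groups". For baseline and week 24 it adds that "the average values of two different samples collected within 1 week will be used to minimize variation between the different urine samples". No such averaging is stated for other visits.

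The Statistical analysis section assigns a model to this endpoint: "analysis of covariance (ANCOVA) using 24 h UP and/or A1C as covariates will be performed to analyze the 24 h UP reduction at 24 weeks". It defines an intention-to-treat set of all randomized participants, so missing week-24 values have to be dealt with. Two consecutive sentences then give the missing-data rules:

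- The first rule calls for imputation: "Multiple imputation analysis will be performed to account for the effect of missing data".
- The second rule, in the sentence directly after it, calls for carrying values forward: "Partially missing data will be carried forward with the principle of the last observation carried forward (LOCF".

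Neither sentence names an endpoint or an analysis set, and neither is called primary or sensitivity. In Table 3 (Study visits and assessment) the row "24 h urinary protein" is ticked at weeks 0, 4, 8, 16, 24, 28, 36 and 48, and is blank at weeks 12 and 20. The Sample size estimation section assumes 20 % dropout.

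**The concern.** The same missing value falls under two rules. A participant measured at weeks 0, 4 and 8 and then lost has data that are, in ordinary language, partially missing. LOCF would fill week 24, and multiple imputation would have almost nothing left to do for that person. The text does not say whether this is intended.

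The two methods rest on different assumptions. LOCF freezes proteinuria at the last reading and enters it as if it had been measured at week 24, so the analysis carries no uncertainty for the filling. Multiple imputation predicts week 24 from the observed visits and carries that uncertainty. With one participant in five expected to drop out, the two can give different primary estimates. If the choice is left open, it could be made after results are known.

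**Working it through.** The plan gives no figure for the effect of missing data, so the check compares the two rules under stated assumptions.

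**Inputs from the protocol article**
- Effect: 0.54, the least-squares mean difference under Sample size estimation. Its unit is not stated; grams are assumed.
- SDs: 0.95 g (TSF) and 0.91 g (placebo). Pooled SD = √[(0.95² + 0.91²)/2] = 0.93 g.
- Dropout: 20 %. The planned size is reproduced as 60 × 1.2 = 72 per arm, 144 in total.
- Latest 24 h UP before week 24: week 16 (Table 3). A carried value is therefore at least 24 − 16 = 8 weeks old.

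**Assumptions, not in the documents**
- The effect builds linearly from zero at baseline.
- In each line below, all dropouts have the same last visit, week w.
- The SD under LOCF stays at 0.93 g.

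**Equal dropout.** LOCF estimate = 0.54 × (0.8 + 0.2 × w/24).

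| Week carried | Factor | Estimate | Loss |
|---|---|---|---|
| 16 | 0.933 | 0.504 g | 7 % |
| 8 | 0.867 | 0.468 g | 13 % |
| 4 | 0.833 | 0.450 g | 17 % |

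**Power, two-sided 0.05 t test.**
- Completers only: 72 × 0.8 = 57.6 per arm at 0.54 g gives 87 %.
- LOCF with 72 per arm: 90 % (0.504 g), 85 % (0.468 g) and 82 % (0.450 g).

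**Unequal dropout.** In an arm with true 24-week change m and dropout d, the LOCF mean is m × [1 − d × (1 − w/24)]. Take week 8 carried, so that 1 − w/24 = 2/3, and assume changes of −0.94 g (TSF) and −0.40 g (placebo), a true difference of −0.54 g.
- Dropout 30 % TSF, 10 % placebo: −0.94 × 0.800 + 0.40 × 0.933 = −0.38 g.
- Dropout 10 % TSF, 30 % placebo: −0.94 × 0.933 + 0.40 × 0.800 = −0.56 g.

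The first split shrinks the effect and the second slightly inflates it.

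**Simulation.** Settings: 72 per arm, visits 0, 4, 8, 16 and 24, dropout at random after week 4, 8 or 16, ANCOVA on baseline, 20 imputations, 600 runs per scenario.
- 20 % dropout in both arms, true difference −0.54 g: LOCF −0.47 g with power 87 to 89 %; multiple imputation −0.54 g with power 88 to 89 %.
- 10 %/30 % splits in either direction: LOCF −0.39 to −0.56 g; multiple imputation −0.54 to −0.55 g. In the worst case (30 % TSF, 10 % placebo, both arms falling) power was 74 % for LOCF and 88 % for multiple imputation.
- No true effect, both arms rising by 0.40 g, 10 %/30 % splits: LOCF shifted by 0.04 to 0.05 g, in either direction.

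**The case against.** The best defence is that the two sentences divide the work: LOCF for isolated gaps, multiple imputation for dropouts. The wording permits this, so it cannot be said that LOCF is bound to govern most dropouts. But the division is not written down. The other reading is at least as natural, so the ambiguity stands. It lies in what the article states and is not detail left to an analysis plan.

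It is also fair that the bias is conditional. The article gives 24-week changes and no trajectories, so linearity is assumed. If values have settled by the last visit, LOCF does no harm. Nor is multiple imputation safe in every case: it was unbiased in the simulation because dropout there was random, and the withdrawal reasons under Participant retention and withdrawal include worsening renal function.

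Two stronger readings are tempting, and the documents do not support them.
- A reader might infer that the time-course analysis is a third competing rule that discards anyone with a missed visit. The text says that "repeated measures analysis of variance (ANOVA) will be applied to determine changes in the 24 h UP and eGFR at each visit". It does not restrict this to complete data, the analysis could be run on imputed data, and it is not the stated week-24 primary comparison. The documents also give no rate of intermittent missingness from which to work out a complete-case fraction.
- A reader might infer a large loss of power by comparing LOCF with a trial in which nobody drops out. No missing-data method can be assumed to recover that power. The fair reference is the completers, at about 87 %.

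**Conclusion.** The concern holds as an unresolved choice between two stated rules, one of which can bias the primary estimate. Under a linear effect and 20 % dropout in both arms, LOCF loses 7 to 17 % of a 0.54 g difference, depending on the week carried. The direction is not fixed once dropout differs between arms, and there is no bias if 24 h UP is stable after the last visit. Power is a minor matter under equal dropout: 82 to 90 % with LOCF against about 87 % for completers, all above the planned 80 %. The case rests on the estimate and on the open choice. Apart from the timing and trajectory assumptions, two facts come directly from the article: the carried value is at least 8 weeks old, and the averaging rule that defines the endpoint does not cover it.

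**What to change.** Before unblinding, name one method for the week-24 change in 24 h UP. Two choices are suitable and broadly equivalent:

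- ANCOVA on baseline 24 h UP after multiple imputation that uses all observed visits.
- A likelihood-based mixed model for repeated measures, with week 24 as the contrast.

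Delete LOCF as a rule for the primary analysis. If it is kept, label it a sensitivity analysis and define what counts as partially missing. A sensitivity analysis for departure from missing at random is a worthwhile option, given the withdrawal reasons listed, but is not needed to resolve the conflict.

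The cost is a change of wording. The article describes the trial as ongoing with 123 patients recruited. No new data or visits are needed, and the methods can be run in the SAS version that the plan names.

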#### Concomitant treatments

Based on the 2013 American Diabetes Association (ADA) practice guidelines, all participants will receive standard treatments as follows:Irbesartan: Irbesartan will be selected as the basic treatment to lower proteinuria and protect renal function. All participants will take irbesartan orally at a dosage of 300 mg daily.Antihypertensive drugs: Participants with hypertension will receive antihypertensive drugs to maintain a blood pressure of ≤ 130/80 mmHg. Non-dihydropyridine calcium channel blockers or alternatively, beta blockers, will be the recommended drugs. If the blood pressure cannot be maintained at 130/80 mmHg by the combination of these two drugs, diuretics will be added.Blood glucose control therapy: The A1C of all participants will be controlled to ≤ 8.0 % throughout the trial. Metformin will be used for participants with eGFR above 60 ml/min. For participants with eGFR below 60 ml/min, oral repaglinide will be the alternative. For participants whose A1C cannot be controlled with oral agents, insulin will be used.Antilipemic agents: Participants with hyperlipidemia will receive atorvastatin.

Participants will also be instructed to follow a low-sodium diabetes diet, including a reasonable intake of calories, protein, carbohydrates, and fat. They will also be asked to exercise regularly. Administration of other medications will be at the discretion of the attending physician investigator and would not interfere with outcome assessments. Investigators will be instructed to record in the CRF the details of any additional/transformational drug or therapy, such as the name, dosage, and duration of administration.

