### Sample size estimation

The sample size was estimated based on results from our preliminary trial. These results found that after a 24-week treatment period, the mean reduction in 24 h UP in the placebo group was 0.40 ± 0.91 g; the mean reduction in 24 h UP in the TSF group was −0.31 ± 0.95 g. The least-squares mean of the difference value between the relative changes from baseline (TSF group-placebo group) was −0.54. The proportion of the cases between the TSF group and placebo group will be 1:1. With 80 % power to detect and a two-sided level of significance of 0.05, the sample size was estimated to be 54 in each group. In order to increase the accuracy of the data obtained, this number was increased to 60. Assuming a dropout rate of 20 %, the final sample size was estimated to be 144.

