### Randomization and concealment

Randomization will be carried out by an independent clinical research organization (CRO) from the Beijing Qihuang Drug Clinical Research Center. The CRO will use a computerized random number generator to produce the randomization schedule employing permuted blocks of random sizes. Participants will be randomly assigned to either the control or the TSF group at a 1:1 allocation. The drug administrator at each participating medical center will enroll patients sequentially based on consultation order. The blocks should provide comparable numbers of participants in both groups at any time in the course of the trial. To ensure concealment, the block sizes will not be disclosed. The randomization list will be retained by the Beijing Qihuang Drug Clinical Research Center for the duration of the study.

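### Lipid changes get an unadjusted t test or rank sum test despite background atorvastatin; the test is valid, but adjusting for the week-0 lipid value would regain precision at no cost

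*Protocol article*

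**What the plan says.** The protocol article's Secondary endpoints section lists change from baseline to 24 weeks in TC, TG, HDL-C and LDL-C. The schedule (Table 3) measures lipids at weeks 0, 4, 8, 16 and 24.

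Under Concomitant treatments, standard care in both arms includes: "Antilipemic agents: Participants with hyperlipidemia will receive atorvastatin". No start time, lipid threshold or stable-dose requirement is given. The eligibility table (Table 2) requires two weeks of irbesartan, controlled blood pressure and an A1C limit before entry, but sets no condition on lipids or lipid drugs. The same section asks investigators to "record in the CRF the details of any additional/transformational drug or therapy".

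Under Statistical analysis, the general rule is "Outcome analysis will be performed using *t* test for normally distributed data and rank sum test for non-normal distribution data". Covariates appear in one place only: "analysis of covariance (ANCOVA) using 24 h UP and/or A1C as covariates will be performed to analyze the 24 h UP reduction". The repeated measures ANOVA covers 24 h UP and eGFR. No model with a baseline term is named for lipids.

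**The concern.** Atorvastatin acts directly on four listed outcomes. Nothing restricts its start to before week 0, and central laboratory results are returned to the sites, so some participants may start it after their baseline lipid value is fixed. Their week-24 change would then contain a statin response, which adds spread to a raw change score. Participants with high baseline lipids would be the likeliest to start, so the week-0 value should predict much of that spread. The plan collects the value but does not use it. It does use baseline adjustment for 24 h UP, on the ground that baseline drives later values, and that reasoning applies to lipids too.

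At stake is how informative the lipid comparison is. The Background section suggests that TSF may work partly through lipid metabolism, so an avoidably imprecise null result would be hard to read.

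**Working it through.** **The plan's own figures.** None exists for lipids. The calculation behind "a two-sided level of significance of 0.05, the sample size was estimated to be 54 in each group" concerns 24 h UP and does not bear on this point.

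**Inputs.** From the protocol: 144 randomized and 20% dropout, so 144 × 0.8 / 2 = 57.6, taken as 58 evaluable per arm; two-sided 0.05. Everything else is assumed: LDL-C mean 3.2 and SD 0.9 mmol/L; week-24 value = 3.2 + 0.7 × (baseline − 3.2) + error with SD 0.6; TSF effect −0.35; statin effect −1.0. A fraction p starts a statin, chosen by a score correlated 0.8 with baseline, by the same rule in both arms.

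**Variance of the raw change.** 0.3² × 0.9² + 0.6² + p(1 − p) × 1.0² + 2 × 0.3 × 1.0 × c, where c is the covariance of baseline with starting: c = 0.9 × 0.8 × φ(z), and z is the upper-p normal point.

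**Residual variance after baseline adjustment.** 0.6² + p(1 − p) × 1.0² − c²/0.9².

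In both cases SE = √(variance × 2/58), and power ≈ Φ(0.35/SE − 1.96).

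- **p = 0.** Raw: 0.0729 + 0.36 = 0.4329, SE 0.122, power 0.82. Adjusted: 0.36, SE 0.111, power 0.88.
- **p = 0.30.** c = 0.72 × 0.3477 = 0.250. Raw: 0.4329 + 0.21 + 0.150 = 0.793, SE 0.165, power 0.56. Adjusted: 0.36 + 0.21 − 0.077 = 0.493, SE 0.130, power 0.77.

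Simulation of the same model (4,000 replicates per scenario; t test on change against ANCOVA on baseline) agrees closely:

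| Starts per arm | t test | ANCOVA |
|---|---|---|
| 0% | 0.816 | 0.875 |
| 15% | 0.643 | 0.793 |
| 30% | 0.556 | 0.752 |
| 50% | 0.517 | 0.734 |

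**Validity.** With equal starts of 30%, the mean raw-change estimate stays at −0.35. With no true effect, the rejection rate is 5 to 6% for both methods.

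**A second set of assumptions.** Baseline SD 1.0, statin effect −1.2, TSF effect −0.4, 72 per arm, statin started by a common baseline threshold. The raw estimate is −0.40. Power is 61% raw and 86% with a baseline term, against 89% and 93% with no starts.

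**Starts driven by on-treatment lipids.** This is a different mechanism.

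- In the first model, if 40% start on placebo and 25% on TSF, the expected raw estimate is −0.35 + (−1.0) × (0.25 − 0.40) = −0.20. ANCOVA also gives −0.20. Power is about 21% for the t test and 33% for ANCOVA.
- In the second model, with starts triggered by on-treatment LDL-C, a true −0.40 becomes −0.26 with or without a baseline term. Adding a term for post-randomization statin use moves it only to −0.28.
- In a check with mid-trial triggers (31% placebo, 17.5% TSF), raw change and ANCOVA both gave −0.21 against a true −0.35. Setting post-start values to missing and imputing them from baseline and the trigger value recovered −0.35. That check used single regression imputation as an approximation.

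**The case against.** A reader might infer three stronger things.

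**That participants are put on atorvastatin during the trial.** The text says only "Participants with hyperlipidemia will receive atorvastatin", as standard treatment. Medical history is taken at week −2 and there is a two-week run-in, so known hyperlipidemia may already be treated by week 0. Starts after baseline are possible, not established.

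**That statin response swamps or masks any TSF effect.** The design argues against this: "Participants will be randomly assigned to either the control or the TSF group at a 1:1 allocation", and "participants and investigators will be blinded to treatment allocation". Prescribing cannot follow knowledge of the arm. With starts that do not depend on arm, the raw contrast is unbiased and estimates the effect of TSF on top of standard care, which is what an add-on trial compares. Attenuation needs starts triggered by on-treatment lipids, and the document describes no such rule.

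**That baseline ANCOVA would cure attenuation.** It does not, as the unequal-start figures show. The precision gain and the attenuation come from different mechanisms and should not be added together.

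Two further objections are fair in part. Some of the gain from ANCOVA is the ordinary benefit of baseline adjustment (82% against 87%) and owes nothing to statins. The trial was also not sized for lipids, so no power commitment is broken.

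The objection that this is detail for an analysis plan does not carry. The protocol does not leave the test open: it names an unadjusted one as the general outcome analysis and confines ANCOVA to 24 h UP.

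**Conclusion.** The point holds as one of precision and interpretation on a secondary endpoint. The named test is valid if statin starts do not depend on arm, but it leaves information in the week-0 lipid value unused. Under the assumed inputs, baseline adjustment is worth about 5 percentage points of power with no statin starts (82% to 87%) and about 19 at 30% starts per arm (56% to 75%). The direction is the same under the second set of assumptions. The sizes depend on the assumed lipid SDs, statin effect, TSF effect and share of starters, none of which the document supplies.

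Attenuation is a separate and conditional concern. It arises only if starts respond to on-treatment lipids that TSF itself changes. Only a tabulation of starts and a supporting analysis address it. Neither issue inflates false positives or bears on the primary endpoint.

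**What to change.** In the Statistical analysis section, replace the unadjusted test for TC, TG, HDL-C and LDL-C with ANCOVA of the week-24 value on arm and the week-0 value, on the log scale where skewed (TG, for example). Lipid-drug use at week 0 may be added as a further covariate. Do not adjust for statin use after randomization, which treatment may itself affect.

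Report lipid-drug starts and dose changes by arm from the CRF. As a supporting analysis only, set lipid values after such a change to missing and multiply impute them, using the baseline and earlier on-treatment lipid values, and state the missing-at-random assumption. This analysis answers a hypothetical question (the effect had lipid treatment not changed) and should be labelled so.

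The cost is analysis wording and some programming. Week-0 lipids and drug details are already collected, and patient care does not change.

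### Creatinine, eGFR, lipids and TCM score at week 24 are tested without adjustment for their own collected baseline, although ANCOVA is already planned for 24 h UP

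*Protocol article*

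**What the plan says.** The Secondary endpoints section defines serum creatinine, eGFR, the four lipids and TCM symptoms as change or improvement between baseline and week 24. Table 3 (Study visits and assessment) ticks all of them at week 0 and week 24; see the row for creatinine and eGFR and the rows "TC, TG, LDL-C, HDL-C" and "Evaluation of TCM syndrome".

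The Statistical analysis section then names three methods that could apply:

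- Default for outcomes: a t test "for normally distributed data and rank sum test for non-normal distribution data". No covariate is named.
- ANCOVA "using 24 h UP and/or A1C as covariates will be performed to analyze the 24 h UP reduction at 24 weeks". No other endpoint is named.
- Repeated measures ANOVA, which "will be applied to determine changes in the 24 h UP and eGFR at each visit". No baseline covariate is named, and creatinine, lipids and TCM score are not covered.

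**The concern.** A change score removes the baseline completely only if the slope of the week-24 value on the baseline value is 1. With any other slope, part of a chance difference between the arms at week 0 stays in the comparison of changes, and the residual variance is larger than it need be. The plan accepts this reasoning for 24 h UP, where it justifies ANCOVA by the importance of baseline, but it does not carry it over to the secondary endpoints, which bear the renal-function, lipid and symptom claims. The randomisation section describes permuted blocks that keep group numbers comparable. It describes no stratification on baseline values that would hold down such imbalance.

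At stake are some precision on these endpoints and the reading of a result that happens to follow a visible baseline difference. The plan also compares baseline data by significance tests without saying what follows from a difference, which invites an adjustment chosen after the fact.

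**Working it through.** **Plan's own figure.** There is none to reproduce: no SD, power or sample size is given for the secondary endpoints. From the Sample size estimation section I take only the 60 per group and the design setting "With 80 % power to detect and a two-sided level of significance of 0.05".

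**Assumed inputs (not in the documents).** rho, the correlation between the week-0 and week-24 values; k, the week-24 SD divided by the baseline SD. The baseline SD is set to 1.

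**Variances per patient.**
- Change score: 1 + k² − 2·rho·k.
- ANCOVA: k²(1 − rho²).
- The difference between them is (1 − rho·k)², which is never negative and is zero when rho·k = 1.
- With k = 1 the ratio ANCOVA/change is (1 − rho²)/[2(1 − rho)] = (1 + rho)/2.

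**Power with equal variances (k = 1).** Take an effect that the t test on change detects with 80 % power, so its standardised size is 1.960 + 0.842 = 2.802. ANCOVA raises this to 2.802/√((1 + rho)/2), and power is approximately Φ(that value − 1.960).

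| rho | variance ratio | standardised effect | ANCOVA power | n per group for the same precision |
|---|---|---|---|---|
| 0.5 | 0.75 | 3.235 | 90 % | 45 |
| 0.7 | 0.85 | 3.039 | 86 % | 51 |
| 0.8 | 0.90 | 2.953 | 84 % | 54 |
| 0.9 | 0.95 | 2.874 | 82 % | 57 |

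A simulation of 4,000 trials at each of rho 0.5, 0.7 and 0.9 gave power of 80 % against 90 %, 79 % against 84 % and 79 % against 81 % (t test against ANCOVA). Type I error was 4.9–5.4 % for the t test and 5.0–5.5 % for ANCOVA, so both are valid.

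**Power when week-24 variance is larger (k > 1).**
- rho 0.5: 90 % at k = 1.0, 85 % at 1.2.
- rho 0.7: 86 % at 1.0, 83 % at 1.1, 81 % at 1.2, 80 % at 1.3.
- rho 0.8: 84 % at 1.0, 81 % at 1.1, 80 % at 1.2.

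Example for rho 0.7, k = 1.2: change 1 + 1.44 − 1.68 = 0.76; ANCOVA 1.44 × 0.51 = 0.734; ratio 0.966; standardised effect 2.850; power 81 %. The gain is about 1 point.

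**Chance imbalance (k = 1).** The baseline difference between arms has standard error √(2/60) = 0.18 SD, so a difference above 0.2 SD in either direction arises in about 27 % of trials for each variable. The change-score comparison carries −(1 − rho) times that difference. The standard error of the change difference is √(2(1 − rho) × 2/60).

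| rho | shift from a 0.2 SD imbalance | standard error of the change difference | shift in standard errors |
|---|---|---|---|
| 0.5 | 0.10 SD | 0.183 SD | 0.55 |
| 0.7 | 0.06 SD | 0.141 SD | 0.42 |
| 0.9 | 0.02 SD | 0.082 SD | 0.24 |

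**The case against.** The best case for the plan is that nothing here is invalid. A t test on change in a 1:1 randomised trial is unbiased over randomisations and keeps its type I error, and the change score already removes part of any imbalance. These are secondary endpoints, and covariates for them are often left to an analysis plan. The first two points stand and limit the weight of this one. The last carries less: the article does not leave the method open but names an unadjusted test, and an analysis plan that followed it would inherit the weakness.

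Four stronger readings are tempting and are not supported:

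- A reader might infer that the secondary comparisons are biased. Any bias is only conditional on an imbalance that has actually occurred.
- A reader might infer that eGFR has no other between-group analysis at week 24. The repeated measures ANOVA includes that visit; what it lacks is a stated baseline covariate.
- A reader might blame the entry rules, which require a minimum of TCM symptoms and cap creatinine. Under randomisation these act on both arms alike, so regression to the mean from selection does not itself create a difference between arms. If entry does narrow the baseline spread, k rises above 1 and, while rho·k stays below 1, the gain from ANCOVA falls.
- A reader might say which endpoints would gain most. The documents give no rho for any of them.

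The power figures also compare ANCOVA with a t test. They do not describe an endpoint that the plan would send to the rank sum test.

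**Conclusion.** The point holds as a loss of efficiency and of protection against chance imbalance, not as an error of validity. It is clearest for creatinine, lipids and TCM score. For eGFR it applies to the week-24 test and to the absence of a named baseline covariate in the repeated measures model.

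The gain ranges from about 10 points of power (rho 0.5, equal variances) to nearly nothing (high rho, or rho·k near 1). That range rests on assumed values of rho and k, 60 analysed per group and a t-test comparator. In large samples the adjusted analysis is never less precise than the change score, so the improvement is worth making even where it is small.

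**What to change.** State in the analysis plan that, for each continuous secondary endpoint, the main week-24 analysis is ANCOVA with treatment and that endpoint's own week-0 value, reported as the adjusted mean difference with 95 % CI. For skewed variables such as triglycerides, use ANCOVA on the log scale and report a ratio of geometric means with 95 % CI (a log analysis does not yield a mean difference), or use a rank-based ANCOVA. Keep the t or rank sum test as supportive.

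The Trial status section reports 123 patients recruited and the Blinding section holds allocation back until the trial ends, apart from emergencies, so this can still be fixed before unblinding. The cost is a change of wording and one degree of freedom per model. No new data are needed.
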